### Outcomes

The primary outcome is postoperative hospital length of stay, defined as the number of days from surgery to hospital discharge. Secondary outcomes include pain trajectories, cumulative opioid consumption at 48 and 72 hours, time to chest drain removal, postoperative complications, opioid-related adverse effects, quality of recovery, health-related quality of life, chronic post thoracotomy pain at 3 and 12 months, ICU stay, and patient satisfaction. Adverse events are monitored and classified according to the Common Terminology Criteria for Adverse Events.

### Sample Size and Statistical Analysis

The sample size calculation was based on a superiority design, assuming a mean difference of 2 days in hospital length of stay between groups, a two-sided alpha of 0.05, and 90% power. Variability estimates were informed by prior literature [29]. A total of 46 participants (23 per group) is required. To account for potential losses and dropouts, a total of 50 participants will be enrolled.

Analyses will follow the intention-to-treat principle, with per-protocol analyses as sensitivity. The primary outcome will be analyzed using negative binomial regression, with adjustment for prespecified covariates, such as age, sex, American Society of Anesthesiologists physical status classification, smoking status, operative duration, and postoperative drain output. Secondary outcomes will be analyzed using appropriate parametric or nonparametric tests, mixed-effects models for repeated measures, and competing-risk analyses where applicable. Missing data will be addressed using multiple imputation. Statistical significance will be defined as a two-sided *P* value <.05. Adjusted analyses will include surgical approach (VATS vs open surgery) and procedure type (major vs minor) as prespecified covariates to account for potential confounding due to surgical heterogeneity.

Length of stay will be analyzed using negative binomial regression due to its expected skewed distribution and potential overdispersion. Although the sample size calculation was based on assumptions of mean differences derived from prior literature, this approach provides an approximation of the anticipated effect size, while negative binomial regression was selected to provide a more appropriate modeling strategy for count-type outcomes..

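### With at least eight covariates in 46–50 patients, an uncorrected negative binomial test exceeds the stated 5% level if length of stay is overdispersed; specify a small-sample-valid test and close the covariate list

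*Protocol article*

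**What the plan says.** All of this is in the protocol article, Sample Size and Statistical Analysis.

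- Model: "The primary outcome will be analyzed using negative binomial regression, with adjustment for prespecified covariates, such as age, sex".
- First covariate list in full: "with adjustment for prespecified covariates, such as age, sex, American Society of Anesthesiologists physical status classification, smoking status, operative duration, and postoperative drain output". The words *such as* leave it open.
- Second list: "Adjusted analyses will include surgical approach (VATS vs open surgery) and procedure type (major vs minor) as prespecified covariates".
- Size: "A total of 46 participants (23 per group) is required", with 50 to be enrolled.
- Level: the design uses "a two-sided alpha of 0.05, and 90% power", and the analysis repeats it: "Statistical significance will be defined as a two-sided" P value below .05.

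The section justifies the model by expecting skewed stays and possible overdispersion. It does not name the estimator, the test, the reference distribution, the mean stay, the SD or the dispersion.

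**The concern.** Maximum likelihood estimates the negative binomial dispersion without allowing for the number of mean coefficients fitted. When that number is large relative to the sample, the dispersion is biased towards zero. Standard errors are then too small, intervals too narrow, and Wald or likelihood-ratio P values too optimistic.

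The count here is intercept 1 + treatment 1 + eight covariates = 10 coefficients, or 12 if ASA and smoking have three levels each, plus the dispersion. At 46 patients that is 46/10 = 4.6 patients per mean coefficient, or 46/12 = 3.8. At stake is whether the trial's primary test has the two-sided 5% level that the plan claims.

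**Working it through.** **1. The plan's own figure.** The SD is not stated, so 23 per group can only be solved backwards. With n = 2(1.960 + 1.282)²·SD²/δ² and δ = 2 days, 23 = 2 × 10.51 × SD²/4, so SD² = 4.38 and SD = 2.09. An exact t calculation needs about 2.05. Going from 46 to 50 corresponds to 8% loss.

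**2. What that SD means for the model.** Negative binomial variance is mean + dispersion × mean². With variance 4.38:
- mean 3: (4.38 − 3)/9 = 0.153
- mean 4: (4.38 − 4)/16 = 0.024
- mean 5 or 6: variance below the mean, so no overdispersion.

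**3. Simulation under a true null.** Treatment was balanced within VATS/open strata. The mean stay was 6 days (assumed), with 4,000 trials per row and a Monte Carlo SE of about 0.5 points. N = 46:

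| Covariate df | True dispersion | Mean estimate | Wald z | Likelihood ratio | Pearson-scaled SE, t |
|---|---|---|---|---|---|
| 8 | 0.1 | 0.043 | 8.8% | 8.3% | 5.2% |
| 8 | 0.2 | 0.114 | 9.4% | 8.5% | 5.1% |
| 8 | 0.4 | 0.270 | 9.6% | 8.6% | 5.8% |
| 8 | 0.8 | 0.575 | 9.6% | 7.9% | 6.1% |
| 10 | 0.1 | 0.034 | 9.4% | 8.8% | 5.0% |
| 10 | 0.2 | 0.097 | 9.7% | 9.1% | 5.2% |
| 10 | 0.4 | 0.241 | 10.3% | 9.4% | 5.6% |
| 10 | 0.8 | 0.528 | 11.8% | 9.5% | 7.3% |

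- At N = 50, Wald gave 8.2–9.2% (8 df) and 9.6–11.0% (10 df). The likelihood ratio went down to 7.3%.
- Runs of 10,000 trials at dispersion 0.4 gave Wald 9.5% (N = 46, 8 df), 9.4% (N = 50, 8 df) and 10.8% (N = 46, 10 df).
- Mean stays of 4 and 8 days (N = 50, 8 df, dispersion 0.2 and 0.4) gave 9.0–9.2%.
- Further ten-coefficient runs at mean 5.5 days and dispersion 0.2–0.4 gave 7.4–10.3%.
- At N = 200 with 8 df the rate was 6.1%, so this is a small-sample effect.
- The fitter agreed with a standard package on the same 1,000 data sets (7.5% against 7.4%; mean dispersion 0.2825 in both).

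**4. Hand check.** The variance of a log mean is proportional to 1/mean + dispersion. At mean 6, with true dispersion 0.40 estimated at 0.27, the ratio is (0.167 + 0.27)/(0.167 + 0.40) = 0.77. The standard error is √0.77 = 0.88 of its proper size. The nominal 1.96 then acts as 1.96 × 0.88 = 1.72, a two-sided error of about 8.5%. Underestimated dispersion explains most of the excess.

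**5. Where the inflation vanishes (N = 50, 8 df, Wald).**
- Poisson data, mean 6: 5.0%.
- SD 2.09 about the fitted mean: 5.4%, 4.1% and 2.7% at mean stays of 4, 5 and 6 days, with the dispersion estimate at zero in 73%, 92% and 98% of trials. At mean 3 it was 8.2%.
- Mean 6 with SD 3 or 4: 8.2% and 9.1%.

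**6. What repairs it.** The scaled test with all eight covariates gave 5.1–6.4% under overdispersion. With 10 df it gave 5.0–5.9% for dispersion up to 0.4, but 7.2–7.3% at 0.8. At SD 2.09 and means of 4–6 days it was conservative (4.1%, 3.2%, 2.1%). A Pearson-scaled Poisson model with t reference gave 5.6–6.3% there. Adjusting only for surgical approach while keeping the ordinary Wald test still gave 6.3–7.3%, so the test does more of the repair than the length of the list.

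**The case against.** The strongest reply is that the article says only negative binomial regression. Estimator, test and small-sample correction are details that an analysis plan commonly settles, and one may exist. That stands: a reader might infer that the plan commits to an uncorrected Wald test, and it does not.

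Second, a reader might infer that the test rejects a true null about 10% of the time whatever the data. The documents do not support this. Mean stay and dispersion are unstated, and the variability implied by 23 per group gives a nominal or conservative test at mean stays of 4–6 days. That also stands, but it does not clear the plan. The article gives possible overdispersion as a reason for the model, and its Limitations section expects mixed procedures and approaches to add variability in length of stay. The implied variance of 4.38 exceeds the mean only if the mean stay is below about 4.4 days, so at longer stays the sample-size assumption and the overdispersion rationale do not fit together.

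Third, the covariates are called prespecified, so a complete list may exist elsewhere. That is possible, but the wording of this article still leaves the list open.

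Fourth, cutting covariates is not needed to control the error rate, and it would remove adjustment that the Discussion and Limitations deliberately plan. That stands.

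**Conclusion.** The point holds conditionally. If length of stay is overdispersed and an uncorrected maximum-likelihood test is used, type I error is about 7–10% with eight single-df covariates and about 9–12% with three-level ASA and smoking, against 5% stated. This rests on assumed mean stays of 4–8 days and dispersion of 0.1–0.8. Without overdispersion, or at an SD of about 2.1 with mean stays of 4–6 days, it is about 3–5%. The actual level thus hangs on a nuisance parameter that the plan does not give.

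A reader might go on to infer that a positive result would be twice as likely to be false. That does not follow. The simulations give the chance of rejecting when there is no effect. The chance that a rejection is false also depends on power and on how plausible an effect was beforehand.

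This should be fixed before analysis starts in September 2027. It does not invalidate the design.

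**What to change.** - State that the primary P value and confidence interval use a small-sample-valid method: a Pearson-scaled standard error with a t reference on n − p degrees of freedom, or a re-randomisation test within the VATS/open strata. The second does not rely on the dispersion estimate for its level. It is the safer choice if ASA and smoking are multi-level and dispersion may be high.
- Delete *such as*, so that one closed list, with the coding of ASA and smoking, defines the primary model.
- Keep surgical approach, the randomisation stratum, in that model.
- Shortening the list is optional. A fuller or shorter model can serve as a sensitivity analysis. Whether variables measured during or after surgery belong in the model is a separate question, not settled here.

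The cost is wording only. Intervals become slightly wider: the t reference alone, with 36 degrees of freedom (46 − 10), replaces 1.960 by 2.028, or 3.5%, and the scaled standard error adds more when the data are overdispersed. Apparent power falls by a few points, because part of it came from the inflated error rate.

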### Ethical Considerations

The study protocol has been reviewed and approved by the Research Ethics Committee of the Escola Paulista de Medicina, Federal University of São Paulo (UNIFESP), in São Paulo, Brazil. Prior to enrollment, all participants are provided with oral and written information regarding the study, and written informed consent is obtained from each participant.

The present trial has been prospectively registered in the Brazilian Registry of Clinical Trials (ReBEC, identifier RBR-78zfpxd) on March 1, 2025, prior to the enrollment of the first participant. The registered title differs slightly from the manuscript title due to administrative constraints, without changes to the study objectives, design, or outcomes. The study is conducted in accordance with the ethical principles of the Declaration of Helsinki, the Brazilian National Health Council Resolution 466/2012, and is reported following the SPIRIT (Standard Protocol Items: Recommendations for Interventional Trials) guidelines for clinical trial protocols. The CONSORT (Consolidated Standards Of Reporting Trials) principles will be followed for the future reporting of trial results.

Study data are collected and managed using REDCap (Research Electronic Data Capture), a secure, web-based platform hosted by UNIFESP. Access to the database is restricted to authorized study personnel, and data are stored in a deidentified format to ensure participant confidentiality. No identifiable personal data will be used in dissemination of the research.

## Results

Ethical approval for this study was obtained in November 2024. Participant recruitment began in July 2025 , and data collection commenced concurrently with recruitment. Follow-up assessments will continue until 12 months after the last enrolled participant, with final data collection expected to be completed by August 2027.

## Discussion

### Overview

Effective postoperative pain management is a cornerstone of enhanced recovery after thoracic surgery [30]. Although thoracic epidural analgesia provides effective analgesia and reduces pulmonary complications, its use is limited by contraindications, side effects, and technical complexity [11-15]. These limitations underscore the necessity to assess alternative analgesic strategies that maintain efficacy while enhancing safety and feasibility [31].

Intercostal cryoanalgesia represents a potential option within multimodal analgesic pathways [20]. Modern cryosurgical systems enable precise, reversible axonal disruption, providing prolonged regional analgesia without indwelling catheters or continuous infusions [6,32,33]. These technical advances address the shortcomings of older studies.

Recent evidence suggests that intercostal cryoanalgesia can effectively reduce postoperative pain intensity, opioid consumption, and length of hospital stay, while enhancing patient satisfaction and functional recovery [1,6,32,33]. Preliminary studies suggest that cryoanalgesia may yield favorable outcomes; however, high-quality randomized evidence comparing this approach with thoracic epidural analgesia remains limited.

By selecting hospital length of stay as the primary outcome, this study captures the integrated clinical impact of postoperative pain control on recovery. However, this outcome is multifactorial and may be influenced by surgical, institutional, and patient-related factors beyond analgesic strategy. Complementary secondary outcomes, including pain trajectories, opioid consumption, quality of recovery, and quality of life, will facilitate a more comprehensive and direct assessment of analgesic effectiveness. In addition, factors such as surgical complications, chest drain management, and discharge practices may influence length of stay. These factors will be accounted for through adjusted analyses including relevant perioperative variables, and through the interpretation of complementary secondary outcomes. Standardized documentation of cryoanalgesia parameters is intended to enhance reproducibility and facilitate future comparative and implementation studies.

Intercostal cryoanalgesia has theoretical and mechanistic features that support its evaluation as part of multimodal postoperative pain management strategies in thoracic surgery, including prolonged regional analgesia during the early postoperative period and the potential to reduce systemic opioid exposure. The systematic documentation of cryotherapy parameters, such as treated intercostal levels, achieved temperatures, and freeze–thaw duration, is intended to enhance reproducibility and enable detailed characterization of technique-related variability. This trial is designed to assess whether intercostal cryoanalgesia achieves postoperative outcomes comparable to those of thoracic epidural analgesia, thereby informing future clinical and implementation studies.

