### Randomization and Blinding

Participants are randomized in a 1:1 ratio to receive either intercostal cryoanalgesia or thoracic epidural analgesia. Randomization is performed using a computer-generated sequence with variable block sizes and stratification by surgical approach (VATS vs open surgery), prepared by an independent investigator. Allocation concealment is ensured using sequentially numbered, opaque, sealed envelopes opened immediately before surgery.

Stratification by surgical approach was implemented to account for potential differences in postoperative pain trajectories and recovery patterns between minimally invasive and open procedures. However, given the overall sample size, the study is not powered for formal interaction testing, and subgroup analyses will be considered exploratory.

Blinding of surgeons, anesthesiologists, and patients is not feasible due to the nature of the interventions. However, outcome assessors and data analysts remain blinded to group allocation, following a Prospective, Randomized, Open, Blinded Endpoint design to minimize assessment bias.

Given the open-label nature of the study and the inclusion of patient-reported outcomes (eg, pain, quality of life, and satisfaction), there is an inherent risk of reporting bias. To mitigate this limitation, outcome assessors and data analysts will remain blinded to treatment allocation, and standardized validated instruments will be used for all patient-reported measures.

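### The Discussion gives the trial a comparability aim, but it is sized and tested only for superiority with no margin, so a non-significant result could not support comparability

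*Protocol article*

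**What the plan says.** In the Discussion (Overview), the article describes the purpose of the trial as follows: "This trial is designed to assess whether intercostal cryoanalgesia achieves postoperative outcomes comparable to those of thoracic epidural analgesia".

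The Methods (Sample Size and Statistical Analysis) set a different hypothesis: "The sample size calculation was based on a superiority design, assuming a mean difference of 2 days in hospital length of stay between groups", with "a two-sided alpha of 0.05, and 90% power". The result is given as "A total of 46 participants (23 per group) is required", and "a total of 50 participants will be enrolled" to allow for losses. No SD is printed; the text says only "Variability estimates were informed by prior literature". The one decision rule in the section is a two-sided P value below .05.

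The Abstract (Objective) and the Introduction both give the primary objective as a comparison of hospital stay between the two techniques. Neither mentions similarity, equivalence or non-inferiority. The article states no margin for any outcome.

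**The concern.** The Discussion sentence is a statement about design, and it does not describe the design in the Methods. A superiority test asks whether the data are incompatible with no difference. A comparability question asks whether the data are incompatible with a difference large enough to matter, and that needs a margin, a rule for comparing the confidence interval with it, and a sample size to match. The article supplies none of these. The sentence also refers to outcomes in general, so it reaches pain, opioid use and complications, for which the article gives no sizing.

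What is at stake is the reading of a non-significant primary result. With this sentence in the published protocol, such a result could be presented as having answered a question the trial was designed to ask, although it would only be a failure to show a difference.

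**Working it through.** **Inputs.** From Sample Size and Statistical Analysis: difference 2 days, two-sided alpha 0.05, power 90%, 23 per arm. From Randomization and Blinding: 1:1 allocation. The SD is not stated and has to be back-solved. SDs of 3 and 4 days are assumptions used to show a range. All calculations use a normal or t approximation to the difference in means; the planned model is an adjusted negative binomial regression.

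**1. The plan's own figure.** n per arm = 2 × (1.960 + 1.282)² × SD² / 2².
- SD 2.05: 2 × 10.51 × 4.2025 / 4 = 22.1, rounded up to 23 per arm, 46 in total.
- SDs from about 2.05 to 2.09 give 23 per arm. With the t distribution, 23 per arm has 90% power at SD 2.046.

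So 46 agrees with an SD of about 2.05, but it cannot be confirmed from stated inputs.

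**2. Precision at the planned size.** Half-width of the 95% interval = t(0.975, 44) × SD × √(2/23) = 2.015 × SD × 0.2949.

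| SD (days) | Half-width, 23 per arm | Half-width, 25 per arm |
|---|---|---|
| 2.05 (back-solved) | 1.22 | 1.17 |
| 3 (assumed) | 1.78 | 1.71 |
| 4 (assumed) | 2.38 | 2.27 |

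A non-significant result has an interval that contains zero, so at least one limit lies at least one half-width from zero. As a share of the 2-day target this is 1.22/2 = 61%, 1.78/2 = 89% and 2.38/2 = 119%. At SD 2.05, a 2-day difference is excluded in both directions only if the estimate lies within 2 − 1.22 = 0.78 days of zero.

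**3. How often a real difference would be non-significant.** Non-central t with 44 degrees of freedom and non-centrality d / (SD × √(2/23)). At SD 2.05 and d = 1, this is 1 / 0.6045 = 1.65.

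| True difference | SD 2.05 | SD 3 (assumed) |
|---|---|---|
| 2 days | 10% | 40% |
| 1.5 days | 32% | 62% |
| 1 day | 63% | 80% |

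**4. What a comparability question would have needed.** The article gives no margin, so the margins here are illustrations only. For non-inferiority with one-sided alpha 0.025, 90% power, true difference 0 and SD 2.05, n per arm = 2 × (2.05 × 3.242 / margin)².
- Margin 2 days: 46 in total.
- Margin 1.5 days: 80 in total; power with 23 per arm about 70%.
- Margin 1 day: 178 in total; power with 23 per arm about 38%.

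On these inputs the planned size would give 90% power only for a margin of about 2 days, which equals the whole superiority effect. The article does not name 2 days, or any other figure, as an acceptable margin.

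**The case against.** The sentence is in the Discussion, and no endpoint, test, sample size or decision rule depends on it. The operative sections are consistent with one another, and the superiority design itself is not faulty. The sentence says that the trial will assess whether outcomes are comparable, which is an open question and not a promised conclusion; the word may have been meant loosely. All of this stands. It limits the point to interpretation and favours a change of wording over a change of design.

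It can also be said that an article need not explain how a null result will be handled, since that may be in an analysis plan that is not shown. That is fair, and the absence of such a rule is not the point. The point is that the article fixes superiority and then ascribes a different question to the same design. An analysis plan elsewhere would not make that sentence match the Methods.

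A reader might go further and infer that a null result is likely, or that it will be reported as comparability. The documents support neither. Under the plan's own assumptions a non-significant result has only 10% probability; higher figures need a smaller true difference or a larger SD. The article does not say how a non-significant result will be described, so misreading is a risk and not a stated intention.

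The figures have limits too. The SD of 2.05 is inferred, and 3 and 4 come from nowhere in the article. At SD 2.05 an estimate near zero would exclude a 2-day difference both ways. The planned model does not estimate a mean difference in days directly.

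**Conclusion.** The point holds as an inconsistency between the Discussion and the Methods. The article attributes to the trial a comparability aim that its design does not contain, and a non-significant superiority test could not meet that aim. With 23 per arm, such a result would leave a difference of at least about 1.2 days unexcluded in one direction or the other at the back-solved SD of 2.05, and about 1.8 or 2.4 days if the SD were 3 or 4. These sizes rest on the inferred or assumed SD and on the t approximation; the textual mismatch does not depend on them. The primary analysis and sample size need no change on this account. The Methods give a 2-day difference without a direction and a two-sided test, so the corrected sentence should not introduce a directional aim such as a shorter stay.

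**What to change.** Reword the Discussion sentence to agree with the Abstract, the Introduction and the Methods. For example: *the trial tests, two-sided and for superiority, whether postoperative stay differs between cryoanalgesia and epidural analgesia*. Then add one sentence: *a non-significant primary result will be reported with its 95% confidence interval as not showing a difference, and will not be interpreted as evidence of comparability or non-inferiority, because no margin was prespecified.*

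The cost is two sentences of wording, with no operational change. The trial gives up a claim that its design cannot support. The change is best made before data analysis begins, which the Abstract puts in September 2027.
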